#### Moderator and mediator analyses

Potential moderators of treatment effects will be investigated using model-based recursive partitioning methods [89]. Model-based recursive partitioning can be used to detect what are called treatment-subgroup interactions. Treatment-subgroup interactions occur when subgroups of patients show differences in the effectiveness (i.e., a better or worse outcome) of one or more interventions. Model-based recursive partitioning can be used to identify these subgroups and their characteristics [90, 91] and ultimately help to tailor treatment to individual patients. These analyses will be explorative in nature and will apply the conservative Bonferroni correction for multiple testing.
(H3) The third hypothesis concerned the relationship between the closeness or perceived similarity of participants with the expert patient they are assigned to, and ED symptomatology, self-efficacy, and experienced social support respectively. The effects of perceived similarity on the three dependent variables will be investigated for the short term (i.e., gains until post-intervention, T1) and the long term (i.e., gains until the last follow-up, T5), resulting in six linear regression analyses that need to be conducted. We correct for multiple testing for these analyses using Holm’s method.(H4) To investigate the fourth hypothesis that changes in self-efficacy during the 8-week intervention period mediate subsequent changes in ED-related symptoms and experienced social support (and not vice versa), a cross-lagged panel design will be used. For self-efficacy and the two outcome variables, change scores will be calculated for pre- (T0) to post-intervention (T1) and for post-intervention (T1) to long-term follow-up (T5; 12 months after T1). Next, hierarchical regressions will be performed, with post-intervention to long-term follow-up change of ED-related symptoms and experienced social support as dependent variables, and pre- to post-intervention change of self-efficacy as the independent variable. Additionally, the inverse relationships will be investigated. In other words, it will be examined whether changes in experienced social support or ED-related symptoms from pre- to post-intervention can predict post-intervention to long-term follow-up changes of self-efficacy. If the initial relationship is significant and the inverse relationship is not, a mediation effect of self-efficacy on ED-related symptoms and/or experienced social support is indicated. Corrections for autocorrelation and synchronous change will be applied to the mediation analysis.

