**Table 2 Tab2:**
[figure not shown]
Overview of assessment occasions and their content

*Note*: The Inclusion of Other in the Self scale (IOS scale; 0.5 min to complete) will be sent at week 3 of the intervention for all participants in a condition with expert-patient support. Attrition follow-up questions will be sent only to participants who do not respond to the assessments

*FU* follow-up, *WCS* Weight Concerns Scale, *SEED* Short Evaluation of Eating Disorders, *PHQ-4* Patient Health Questionnaire, *EDE-Q* Eating Disorder Examination Questionnaire, *GSES* General Self-Efficacy Scale, *SSL* Social Support List, *RSES* Rosenberg Self-Esteem Scale, *EQ-5D-5 L* EuroQol five dimensions, five levels generic health index, *ICECAP-A* ICEpop CAPability measure for Adults, *TiC-P MIDI* Trimbos/iMTA questionnaire for Costs associated with Psychiatric Illness Midi version, *PCQ* Productivity Costs Questionnaire

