##### Inclusion of Other in the Self scale

The Inclusion of Other in the Self scale (IOS scale [77]) will be sent to participants allocated to one of the conditions with support by an expert patient at week 3 of the intervention to assess perceived similarity and feelings of closeness early in the working relationship between expert patient and participant. The IOS scale is a one-item instrument in which seven images with two circles representing the self and the other that overlap increasingly, from zero overlap to almost complete overlap, are presented to participants. The participants can then rate their relationship with another person by choosing the best fitting image. More overlap between the circles indicates a closer bond. This scale is particularly suited for the current study, since it can be used for any type of relationship, and not only romantic partners, friends, and acquaintances [78]. Furthermore, Gächter, Starmer, and Tufano [79] conducted three studies to examine the validity and reliability of the IOS scale. A very strong convergent validity with a closeness index derived from six other relationship inventories (Spearman correlation of 0.85) was found. The authors conclude that the one-item IOS scale is easy to use, highly reliable, and a very powerful measure of closeness of relationships.

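### H3 counts change from before week 3, when similarity is first measured, as support for an effect of similarity

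*Protocol article*

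**What the plan says.** The section on moderator and mediator analyses introduces H3 as a relationship between perceived similarity and three outcomes: ED symptomatology, self-efficacy and experienced social support. It then turns to causal wording: "The effects of perceived similarity on the three dependent variables will be investigated for the short term" and likewise for the long term. The short-term outcome is "gains until post-intervention, T1" and the long-term one "gains until the last follow-up, T5". The starting point of the gains is not spelled out. The count is "resulting in six linear regression analyses that need to be conducted", and the only safeguard named is multiplicity: "We correct for multiple testing for these analyses using Holm’s method". No covariates are listed for H3, either as included or as left out.

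The predictor is the one-item Inclusion of Other in the Self (IOS) scale. Its section says that it is sent "at week 3 of the intervention to assess perceived similarity and feelings of closeness early in the working relationship". The note to Table 2 adds that it "will be sent at week 3 of the intervention for all participants in a condition with expert-patient support", so two of the four arms supply data. The Design section puts T1, the first assessment after baseline that the text describes, at 8 weeks.

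Under Aims and research questions, H3 is one of two hypotheses set apart from the exploratory tests of the second aim.

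**The concern.** A predictor measured at week 3 cannot have produced change that took place before week 3. T1 is the first post-baseline assessment described, so a gain up to T1 can hardly start anywhere but T0. Both outcomes therefore contain about three weeks of change that precede the predictor. A participant who is already improving may rate the bond as closer, and the regression would credit that improvement to similarity.

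The article takes care over time order for H4. There, T0–T1 change predicts later T1–T5 change, the inverse relation is tested, and corrections for autocorrelation and synchronous change are announced, but only for the mediation analysis. H3 has no comparable step. At stake is a stated hypothesis about how expert patients help: reversed order could be reported as confirmation. Holm's method limits chance findings across the six tests and has no bearing on the direction of an association.

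**Working it through.** **Reproducing the plan's count.** 3 outcomes × 2 horizons = 6 models, as stated. Six leaves no room for separate models per support arm, so the two arms are analysed together.

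**Inputs from the article (Sample size calculation; Statistical analyses).** 88 per condition, so 2 × 88 = 176 in the two support arms. With 25% dropout by T1, 176 × 0.75 = 132. T0–T1 correlation 0.5. Two-sided alpha 0.05. The 0.5 was assumed for the trial's sample size; using it for all three outcomes is my extension.

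**Assumptions not in the article.**
- Scores are standardised with equal variance at T0 and T1.
- 3/8 of the residual variance at T1 arises in weeks 0 to 3.
- Similarity has no effect on outcome. It correlates q = 0.1, 0.2 or 0.3 with that early component, and in this first scenario has no relation to baseline.

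**Gain without the T0 score.** Residual variance at T1 given T0 is 1 − 0.5² = 0.75. Var(gain) = 2 − 2 × 0.5 = 1. The correlation of similarity with gain is q × √(0.75 × 3/8) = 0.530q, that is 0.053, 0.106, 0.159. Fisher's z with n = 132 gives rejection rates of 9.3%, 22.7% and 44.5%. Simulation with 3,000 trials per setting gave 9.5%, 22.1% and 44.8%.

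**Gain with the T0 score added.** The partial correlation is q × √(3/8) = 0.612q, that is 0.061, 0.122, 0.184. Fisher's z gives 10.7%, 28.6% and 55.7%; simulation gave 11.6%, 28.3% and 56.2%. Adjustment removes baseline noise but not the early change, so the false signal stands out slightly more.

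**Other settings (simulation).**

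| Setting | Without T0 score | With T0 score |
|---|---|---|
| n = 176, q = 0.1 / 0.2 / 0.3 | 11.8 / 27.9 / 57.2% | 13.5 / 36.2 / 68.6% |
| n = 132, q = 0.2, Holm's first step (0.05/6 = 0.0083) | 7.3% | 10.0% |
| n = 176, q = 0.2, Holm's first step | 10.7% | 14.9% |
| n = 132, q = 0 | 4.6% | 4.7% |

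When change was counted only from week 3 and adjusted for the week-3 score, rejection stayed at 4.4% to 6.0% in every setting. The article describes no EDE-Q, self-efficacy or social support score at week 3, so that model cannot be fitted from what is shown.

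**Starting score: both forms can mislead.** Now let similarity relate to baseline instead of early change, with correlation 0.1, 0.2 or 0.3 (assumed), n = 132.
- *Similarity tied to T1 only through the T0 score.* Without the T0 score, the correlation with gain is half the assumed one. Simulated rejection is 8.5%, 21.0% and 40.9%. Adding the T0 score returns it to 5.3%, 5.5% and 5.0%.
- *Similarity tied to a stable trait behind both T0 and T1.* Without the T0 score, rejection is 4.8%, 4.4% and 5.4%. Adding it raises rejection to 10.0%, 26.7% and 53.4%. For correlation r, the partial correlation is 0.5r/√(0.75(1 − r²)), which is 0.182 at r = 0.3; Fisher's z gives 54.7%.

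The article gives no ground for choosing between these two structures.

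**The case against.** Felt similarity cannot be measured before contact, and the article says that week 3 was chosen to capture the working relationship early. No outcome score at week 3 is described, so some overlap is an ordinary limit of process research. That stands as a reason for the timing. It does not justify calling the result an effect when T1–T5 data, which follow the predictor, will be collected anyway.

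The size rests on assumed correlations. The sign is open too: with −0.2 for baseline and +0.2 for early improvement, the two biases nearly cancel without the T0 score (4.8% to 5.4% rejection). The rates are per test before Holm, and 132 is a complete-case number although multiple imputation is planned. All of this stands, and it makes the figures an illustration of vulnerability rather than a forecast.

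A reader might infer that H3 uses raw gains with baseline score and condition left out, and that baseline adjustment is the remedy. The article supports neither. It is silent on covariates, which a condensed article may leave to a fuller document. For a predictor that is not randomised, adjustment removes bias under one structure and creates it under another.

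The post-T1 check also has limits: it skips weeks 3 to 8, most of the support period, and its adjusted form conditions on a T1 score that similarity may already have influenced. It settles the order of measurement, not confounding.

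**Conclusion.** The point holds as one of time order. With gains read from T0, the H3 outcomes include change that precedes the predictor, the text calls the resulting associations effects, and neither Holm's method nor the T0 score addresses this. Under the assumed correlations of 0.1 to 0.3 with early improvement, false support per test at n = 132 is about 9% to 45% before Holm. At Holm's first step it is about 7% for a correlation of 0.2, against a nominal 0.8%. If similarity is unrelated to both early change and baseline, there is no inflation.

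On starting score and condition, the supportable statement is only that no adjustment is specified. The matter is minor for the trial as a whole: H3 is a secondary hypothesis and the primary T0–T1 comparison does not depend on it.

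**What to change.** 1. State that the H3 gains start at T0, and keep the six models with Holm's correction.
2. Include randomised condition (with or without Featback) as a covariate, since the two support arms are pooled and H2 expects them to differ.
3. Report each model with and without the T0 score of the same outcome, as a sensitivity pair with neither taken as correct by default.
4. For each of the three outcomes, add a T1-to-T5 regression on week-3 similarity, given both as T1–T5 change and as the T5 score adjusted for T1. Claim that similarity precedes improvement only if these agree with the main models.
5. Write associations where the H3 text now says effects.

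No new data are needed. The cost is a few more regressions and somewhat longer reporting. The post-T1 check leaves out any effect of similarity between week 3 and T1, so a null result there would not refute H3 in the short term.

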### Aims and research questions

The current study builds on the study by Aardoom et al. [20] by investigating whether the results regarding the effectiveness of Featback will hold. More specifically, the first aim is to investigate the (cost-)effectiveness of the Internet-based intervention Featback in comparison to Featback with support from an expert patient, support from an expert patient without Featback, and a waiting list control condition (WLC). The primary outcome measures of the current study are ED-related attitudes. Secondary outcome measures include self-efficacy, social support, symptoms of depression and anxiety, motivation to change, user satisfaction, intervention usage, and help-seeking attitudes and behaviors. Finally, cost-effectiveness will be evaluated through the reported quality of life, outcomes for patients in terms of capabilities, and medical and societal costs. We have two hypotheses accompanying the first research aim.
 Our primary hypothesis is that Featback without expert-patient support, Featback with expert-patient support, and expert-patient support without Featback will be more effective in reducing ED psychopathology and more cost-effective compared to a waiting list. Secondly, we hypothesize that the combination of expert-patient support plus an online intervention will be more effective in reducing ED psychopathology and more cost-effective compared to expert-patient support or Featback only and that the improved effectiveness will be maintained up until a year later.

The second aim of this study is to investigate predictors and moderators of intervention response to explore what works for whom. Predictors and moderators that will be tested as predictors or moderators of treatment response and/or intervention usage are age, gender, and educational level, motivation to change, social support, severity of ED symptoms, severity of symptoms of depression and anxiety, self-efficacy, self-esteem, and closeness or perceived similarity of participants with expert patients. Additionally, self-efficacy is examined as a mediator. Besides the exploratory tests, there are two hypotheses concerning the second aim of this study.

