(H3) Since a perceived similarity of participants to expert patients might enhance the receptivity and self-efficacy of participants, it is hypothesized that participants who feel more similar to the expert patient they are assigned to have better outcomes in terms of ED symptomatology, self-efficacy, and experienced social support.(H4) It is hypothesized that, since the effectiveness of expert patients is theorized to come from effectively improving self-efficacy, changes in self-efficacy during the intervention period mediate subsequent long-term effects of the intervention on ED-related symptoms and experienced social support.

Thirdly, we aim to investigate practical experiences with Featback, such as intervention usage and user satisfaction.
(H5) It is expected that Featback with weekly expert-patient support will enhance intervention usage as well as satisfaction with the intervention compared to Featback alone.

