### Sample size calculation

An a priori statistical power analysis was conducted in G*Power version 3.1 to determine the optimal sample size having 80% power to detect a small effect size (*f* = 0.15, which corresponds to *d* = 0.30) between the active intervention conditions on the one hand and the control condition on the other. Consequently, the sample size calculation was based on a between-factors repeated measures analysis of variance (ANOVA) with two groups and two measurements (i.e., baseline and post-intervention; T0–T1). A significance level of α = 0.05 was maintained. The effect size was based on data from a previous RCT [20]. Calculations indicated a total of 264 participants will be needed, meaning 88 participants per condition. We assume a Pearson correlation of 0.5 between the outcome variable on baseline and post-intervention (i.e., T0–T1), which explains 25% of the variance of the outcome variable. Therefore, the sample size per group can be reduced by 25%. However, adjusting for an anticipated dropout rate between T0 and T1 of 25% (based on previous data), we will still need 88 participants per condition (*N* = 352). The high dropout rate introduces a risk of bias through selective dropout. However, participants in the previous Featback trial [20] who dropped out during the intervention did not differ from those who did not drop out with regard to ED psychopathology, ED quality of life, comorbid anxiety or depression, age, weight, hours spent online, allocated condition, and duration of their eating problems. Hence, bias because of selective dropout in the current sample is, at least based on these variables, improbable.

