### Statistical analyses

All statistical analyses will be conducted in SPSS version 25 and the R statistical programming environment [85]. A two-tailed significance level of *α* = .05 will be maintained throughout the analyses unless indicated otherwise. All analyses will be conducted according to the intention-to-treat (ITT) approach. This means that all participants who underwent randomization, even those who withdrew from the study or deviated from the protocol, are included in the analyses. For the effectiveness analyses, both ITT and completers analyses will be conducted. A participant is considered a completer when he/she has completed at least five monitoring assessments (i.e., Featback only condition), five support sessions (i.e., expert-patient support only condition), or both (i.e., Featback plus expert-patient support condition).

Missing data will be handled using multiple imputation [86]. Multiple imputations using predictive mean matching will be conducted in the statistical programming environment R [85]. Interactions will be taken into account in the imputation procedure [87]. Multiple imputation methods have several advantages over complete-case analyses or single imputation techniques and are therefore highly recommended [86, 88].

Homogeneity of groups (i.e., between-group differences) will be assessed at baseline (T0) using chi-square tests for categorical variables and ANOVAs for continuous variables. Additionally, homogeneity of variances will be assessed using Levene’s statistic, and non-parametric testing will be used when appropriate.

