#### Intervention effectiveness analyses

To investigate the effectiveness of Featback with and without weekly expert-patient support, within-group and between-group effect sizes (Cohen’s *d*) will be calculated (i.e., the effects of time and intervention) using the pooled standard deviation of each group. We are mainly interested in the effect from baseline to post-intervention (T0–T1), but to see if effects are maintained over the short and long term, analyses will be repeated for T1–T3 and T1–T5 respectively.
 To answer the first and main hypothesis that the active interventions (i.e., Featback, expert-patient support, and Featback plus expert-patient support) are more effective than a waiting list in reducing ED symptomatology (i.e., primary outcome EDE-Q global score), the three active intervention conditions will be compared to the waiting list condition. Repeated measures ANOVA will be used for T0–T1 to test this hypothesis. To see if the effects are maintained, these analyses are repeated for T1–T3 and T1–T5. The second hypothesis was that the combination of Featback and expert-patient support would be more effective than Featback or expert-patient support alone. A repeated measures ANOVA with post hoc tests will be conducted to compare T0–T1 differences in ED symptomatology between the four conditions. The post hoc analyses apply the Bonferroni correction for multiple testing. To see if these effects are maintained, these analyses are repeated for T1–T3 and T1–T5.

These confirmatory analyses will be repeated controlling for significant baseline variables (i.e., age, duration of ED psychopathology, number of psychological healthcare appointments). Additionally, the main analyses will be repeated for completers only.

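### H4 asks whether self-efficacy mediates the long-term effect, but its regressions see only further change from T1 to T5, so a mediated effect that is gained by T1 and then kept goes undetected

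*Protocol article*

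**What the plan says.** Under Aims and research questions, H4 is that self-efficacy change during the intervention will "mediate subsequent long-term effects of the intervention on ED-related symptoms and experienced social support". Under Moderator and mediator analyses, the aim is reworded as mediation of later changes in the two outcomes, and not the reverse. Change scores are formed for T0-T1 and for T1-T5. The hierarchical regressions are run "with post-intervention to long-term follow-up change of ED-related symptoms and experienced social support as dependent variables", with T0-T1 self-efficacy change as the predictor. The inverse regressions predict T1-T5 self-efficacy change from T0-T1 outcome change. Mediation is declared if the forward relation is significant and the inverse is not, with corrections for autocorrelation and synchronous change. No sign is required of the forward slope, and the general rule is two-sided: "A two-tailed significance level of *α* = .05 will be maintained throughout the analyses".

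The plan also says when it expects the effect. Under Intervention effectiveness analyses: "We are mainly interested in the effect from baseline to post-intervention", with T1-T3 and T1-T5 analysed to see whether effects last. H2 adds, for the combination against its single components, that "the improved effectiveness will be maintained up until a year later".

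**The concern.** The T1-T5 window serves two purposes. In the effectiveness analyses, little change between groups there is the desired result, because it shows that the effect was kept. In H4 it is the only outcome in which mediation can appear. A benefit that self-efficacy brings about within the eight weeks and that then persists for a year fits the wording of H4, but lies outside the window its analysis examines.

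H4 tests the mechanism the article proposes for expert-patient support. A null result would invite the conclusion that self-efficacy is not how such support works, even where it carried the whole effect. The missing sign creates the opposite risk: participants whose self-efficacy rose most may lose most of their symptom gain after T1, and that significant slope would count as mediation.

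**Working it through.** **The plan's own figure.** The only power statement is for the T0-T1 comparison: "having 80% power to detect a small effect size", for a "repeated measures analysis of variance (ANOVA) with two groups and two measurements". With f = 0.15, correlation 0.5 and m = 2 measurements, the noncentrality is f²·N·m/(1 + (m - 1)·0.5) = 0.0225 × 264 × 2/1.5 = 7.92, which gives power 0.80 at N = 264. The stated total reproduces. No power is given for H4. Below, 264 is also the number left of 352 after 25% dropout (352 × 0.75), and 176 is half of 352, an assumed lower case for T5.

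**Effect in the analysed window.** The intervention effect on T1-T5 change equals the effect at T5 minus the effect at T1. With the planned d = 0.30 at both times this is 0.30 - 0.30 = 0. The same holds for any effect that is exactly maintained.

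**Chance of meeting the rule when both lagged slopes are zero.** Per outcome: 0.05 × 0.95 = 4.75%. For at least one of two outcomes, taken as independent: 1 - 0.9525² = 9.3%. Counting only the expected direction: 0.025 × 0.95 = 2.4% per outcome.

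**Simulation.** The slopes and SDs are assumptions; the article gives none. X is support (half of the sample).

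- T0-T1: ΔS₁ = 0.5·X + e and ΔE₁ = -0.6·ΔS₁ + e, so the whole 0.30 effect runs through self-efficacy (0.5 × 0.6 = 0.30).
- T1-T5: ΔE₂ = -0.6·ΔS₂ + λ·ΔS₁ + e, where ΔS₂ is pure error.
- Every error SD is 0.8 and there is no measurement error.
- Forward regression: ΔE₂ on ΔS₁, ΔE₁ and ΔS₂. Inverse regression: ΔS₂ on ΔE₁, ΔS₁ and ΔE₂.

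| After T1 | λ | Rule met, n = 264 |
|---|---|---|
| Effect exactly kept | 0 | 4-5% (about 4-5% at n = 176 too) |
| Self-efficacy gain acts further | -0.2 | about 79% |
| 30% of the effect fades | +0.3 × 0.6 = +0.18 | about 69%, forward slope in the wrong direction |

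**Sensitivity to the assumptions.** A second set used self-efficacy-change SD 0.7, an active-arm gain of 0.3, slope -0.5, and residual and drift SDs of 0.5.

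- Exact maintenance, unadjusted or with error-free measures: rule met in 4-6% of trials at n = 352, 264 and 176.
- Exact maintenance, with the planned corrections and reliability 0.8-0.9: rule met in 17-28%. These extra detections are measurement-error artefacts, since the true lagged slope is still zero. The article quotes an alpha of 0.75 to 0.91 for the self-efficacy scale.
- Lagged slope -0.2, n = 264: 95% unadjusted; 70% with corrections at reliability 0.9.
- 30% fading, n = 264: 89% unadjusted; 5% with corrections at reliability 0.9.

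**What a T0-anchored model would see.** Consider a model for the T5 score adjusted for T0, with support and T0-T1 self-efficacy change. In fully mediated, maintained data (error SD 0.8, support shifting self-efficacy by 0.3 or 0.5) it finds both mediation paths in 86% to over 99% of trials at n = 264 and in 71% to 98% at n = 176. It does not show direction. When symptom change drives self-efficacy and not the reverse (slopes -0.6 and -1.0, n = 264), the same test declares mediation in 34-59% of trials, against about 4% for the plan's rule. With a shared influence on both variables within the period it does so in over 99%.

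**The case against.** The strongest defence is that H4 speaks of subsequent effects and the analysis section of subsequent changes. Predicting T1-T5 change from T0-T1 change is a natural reading, and it secures temporal order. On that reading a world with no lagged effect is one in which H4 is false, and a 5% rejection rate is correct error control. This stands as a reason to keep the lagged regressions. It does not remove the mismatch with the aims section, which names long-term effects of the intervention; nor does it prevent a null from being over-read.

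A reader might infer that H2 and H4 contradict each other, so that both can hold only if the effect keeps growing after T1. The document does not support that. H2 concerns group means, for the combination against single components on ED psychopathology; H4's regressions work at the level of persons. With a constant group effect of 0.30, a later self-efficacy slope of -0.2 and an offsetting loss of other benefit, the forward test was significant in about 73% of trials at n = 264. For social support, the other H4 outcome, H2 states no maintenance expectation.

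A reader might also infer that the T1-T5 outcome should be replaced. The reverse-causation results show why not: a T0-anchored outcome is partly concurrent with the mediator.

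**Conclusion.** The concern holds as a mismatch between the H4 hypothesis and the window its analysis covers. When the effect is carried by self-efficacy by T1 and exactly maintained, the rule is met at about the alpha level, 4-5% per outcome, given no lagged effect and error-free measures. It is tempting to read this as H4 being missed 95% of the time. That figure is simply 1 minus alpha in this one scenario and is not a general miss rate: a continuing action of self-efficacy after T1 is found in roughly 70-95% of trials under the assumptions tried.

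The absent sign is a separate weakness. The chance of declaring mediation from fading gains ranged from 5% to 89%, depending on adjustment and measurement error. H4 is a secondary mechanism question, and the primary T0-T1 comparison is untouched. The change is still worth making because it decides what a null H4 may be taken to mean.

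**What to change.** In Moderator and mediator analyses (H4):

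1. Keep the T1-T5 cross-lagged regressions as the test of direction, and require the forward slope to lie in the expected direction before mediation is declared.
2. Add, without substituting, a mediation model for the T5 score (EDE-Q global; social support) adjusted for its T0 score, with the expert-patient-support factor and T0-T1 self-efficacy change. Report the indirect effect with a bootstrap interval.
3. State that the lagged regressions test only further change after T1, so a null there does not speak against mediation of a maintained effect.
4. State that the T0-anchored model alone does not establish direction, because part of its outcome is concurrent with the mediator.

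The cost is wording and a few extra models on T0, T1 and T5 data already planned. The downside is that the added result is open to reverse causation and shared influences, so it must be read together with the lagged analysis.
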